## Abstract

**Background:**

Peripheral arterial disease (PAD) has a population prevalence of 4.6% with intermittent claudication (IC) presenting as one of the earliest and most common symptoms. PAD has detrimental effects on patients’ walking ability in terms of maximum walking distance (MWD) and pain-free walking distance (PFWD). Research has suggested extracorporeal shockwave therapy (ESWT) may induce angiogenesis in treated tissue; therefore, our objective is to assess the tolerability and efficacy of ESWT as a novel treatment of intermittent claudication.

**Methods/design:**

Patients with unilateral claudication will be randomised to receive either ESWT (PiezoWave 2 shockwave system) or sham treatment to the calf muscle bulk three times per week for 3 weeks. All patients are blinded to treatment group, and all assessments will be performed by a masked assessor. Treatment tolerability using a visual analogue scale, ankle-brachial pressure index, MWD, PFWD and safety will all be formally assessed as outcome measures at baseline and at 4, 8 and 12 weeks follow-up.

**Discussion:**

This trial will be the first of its kind in terms of methodology in relation to ESWT for intermittent claudication. A double-masked randomised controlled trial will provide useful information about the potential for the use of ESWT as a non-invasive treatment option and the need for further robust research.

**Trial registration:**

ClinicalTrials.gov, NCT02652078. Registered on 17 October 2014.

**Electronic supplementary material:**

The online version of this article (doi:10.1186/s13063-017-1844-4) contains supplementary material, which is available to authorized users.

## Introduction

Peripheral arterial disease (PAD) is common in western society with a prevalence estimated at 20% of those aged over 60 [1]. Intermittent claudication (IC), a manifestation of PAD in the lower limbs, causes sufferers to experience cramping pain in the affected muscles, most commonly the calves, which occurs after walking a short distance and increases in intensity until the person stops, where the pain then gradually subsides. PAD can be limiting or occasionally debilitating and has been shown to have considerable deleterious effects on patients’ quality of life [2].

There is a 15-fold increase in mortality secondary to cardiovascular disease in symptomatic patients with severe large vessel PAD; therefore, treatment is based around minimising cardiovascular risk factors and reducing risk of disease progression [3]. With conservative management strategies a proportion of patients will remain with stable symptoms, whilst a minority will deteriorate and require intervention in the form of an endovascular or open vascular surgical procedure.

The physiological negative effects caused by PAD are hypothesised to be due in part to recurrent episodes of ischaemia-reperfusion injury (IRI), which occurs as claudicants exercise (ischaemia) and rest (reperfusion). IRI causes progression of atherosclerosis, as well as endothelial dysfunction and end organ damage [4–6]. During ischaemic episodes and subsequent reperfusion, leucocytes become activated, resulting in release of proteolytic enzymes, cytokines and reactive oxygen species [7, 8].

## Background

A shockwave is described as a transient short-term acoustic pulse with a high peak pressure. This waveform generation and rise to peak pressure occur within nanoseconds [9]. Biological effects of shockwaves on human tissue were first documented during World War II when severe lung injuries secondary to water bombs were noted within casualties who did not display any evidence of external injury [10]. The medicinal use of high energy extracorporeal shockwaves did not develop until the 1980s, when they were targeted to fragment urinary stones (lithotripsy); results led to this technique becoming the gold standard treatment option for urolithiasis [9]. From this point the developing use of extracorporeal shockwave therapy (ESWT) followed an interesting course which started after an incidental finding of iliac bone thickening in patients undergoing lithotripsy, which proposed the potential osteoblastic effect of shockwave therapy [11]. Researchers confirmed these observations through a number of clinical trials using shockwave therapy on delayed non-union fractures [12–14]. Observational improvements to soft tissue wounds overlying these fractures treated with ESWT then encouraged research into the benefits of shockwave therapy in hard-to-heal chronic soft tissue wounds [15].

The exact mechanism of action of ESWT on soft tissue is not fully understood, although the principle of mechanotransduction is thought to be responsible for the biological changes that take place. Mechanotransduction is the transfer of mechanical stimuli into chemical signals; this takes place at a cellular level where mechanosensory components within the cell wall are stimulated, which activates gene expression of growth factors and cytokines as well as cell proliferation or differentiation [16]. The mechanical force is a secondary effect of cavitation which can be visualised in water by the creation of cavitation bubbles that then emit secondary shockwaves. This physical force can also be seen when shockwaves are directed over a thin aluminium foil, which show the effect of cavitation bubbles collapsing on or near the foil [17].

Increased expression of growth factors such as endothelial nitric oxide synthase (eNOS) and vascular endothelial growth factors (VEGFs) have been demonstrated following treatment of soft tissues with ESWT during various studies both in vivo and in vitro. However, the majority of this evidence is from animal studies, and further investigation is required [18–21].

Due to these findings, further applications of ESWT are beginning to be explored. One such application included the use of ESWT to treat ischaemic heart disease where focussed shockwaves were directed at ischaemic areas of myocardium. This demonstrated some positive findings with notable results including improvement in left ventricular ejection fraction (LVEF), ventricular wall thickening, reduced symptoms, reduced nitroglycerine use and again increased upregulation of growth factors and angiogenesis [22]. A further use has potentially been found with small trials commencing in ESWT for peripheral vascular disease, which has led to the development of this current protocol.

### Summary of current evidence

To date, four studies have investigated ESWT in claudicants (Table 1). They include one randomised control trial of 22 patients with 12 patients receiving treatment and 10 receiving a sham control. This study targeted ESWT at a stenotic plaque lesion within lower limb arteries and demonstrated significant reduction in degree of arterial stenosis, significant improvement in pain-free walking distance (PFWD) and reduction in pain severity. These findings were also coupled with a significant reduction in Fontaine staging [23].

**Table 1 Tab1:** Human studies related to ESWT for peripheral arterial disease

Study/author(s)	Type	Sample size	Methods	Significant results	Limitations
Ciccone MM, Notarnicola A [23]	Randomised control trial	*N* = 22, cases = 12, controls =10	4 sessions at 1 weekly intervals, 2000 impulses, 0.03 mJ/mm^2^. Aimed at stenotic lesion	Increased *pain-free walking distance* and reduction in pain severity. Reduction in degree of arterial stenosis. Reduced Fontaine staging	Small sample size, short-term follow-up
Tara S, Miyamoto M [24]	Prospective non-randomised pilot study	*N* = 10	6 sessions (3 times per week for 2 weeks). 6 spots per session (300 impulses/spot) 0.11–0.12 cmJ/mm^2^	No adverse events. Improved transcutaneous oxygen tension (TcPO_2_) in both calf and dorsum of foot. Scintography demonstrated improved perfusion in dorsum of foot only	Small sample size, non-randomised, short-term follow-up
Belcaro G, Cesarone MR [25]	Prospective non- randomised	*N* = 32	6 sessions (3 times per week for 2 weeks) 1000 impulses per session, 0.08–0.43 mJ/mm^2^	Improved *pain-free walking distance*, analogue scale for pain, laser Doppler skin perfusion, partial pressure of oxygen and decreased partial pressure of carbon dioxide. Reduced ORACLE score	Small sample size, non-randomised short-term follow-up
Serizawa F, Ito K [26]	Prospective non-randomised	*N* = 12	9 sessions (3 times per week for 3 weeks) 40 spots per session with 200 impulses/spot 0.1 mJ/mm^2^	Improved *maximum walking distance*, walking impairment questionnaire scores and shorter recovery time	Small sample size, non-randomised, short-term follow-up
Serizawa F, Ito K [26]	Prospective non-randomised	*N* = 6	6 sessions (3 times in first week (days 1, 3 and 5) and 3 sessions in week 5 (days 29, 31, 33) 40 spots per session with 200 impulses/spot 0.1 mJ/mm^2^	The *maximum walking distance* was significantly increased at 4 weeks and 8 weeks follow-up	Small sample size, non-randomised, short-term follow-up

Data captured in italic are significant outcome for measures in the trial protocol

Another study was a small prospective non-randomised pilot study of 10 patients which aimed to prove safety; its primary end point was observation of adverse events. This study found no adverse events secondary to shockwave therapy. The secondary end point was a measure of tissue perfusion using scintography, laser Doppler and measurement of transcutaneous oxygen tension (TcPO_2_). The use of scintography demonstrated significantly improved tissue perfusion in the dorsum of the foot; however, perfusion was unchanged in the lower leg region. Maximum TcPO_2_ increased significantly in both the calf region and dorsum of the foot. Skin perfusion pressure measured using the laser Doppler showed increases in both regions, but neither was significant [24].

Another prospective study of 32 patients underwent EWST for critical limb ischaemia with both rest pain and localised distal necrosis. Outcomes included PFWD, visual analogue scale (VAS) for pain, laser Doppler skin perfusion, partial pressure of oxygen and partial pressure of carbon dioxide. All of these outcomes demonstrated significantly improved measurements [25].

Finally a further two prospective non-randomised trials by Serizawa et al. with a total of 6 patients and then 12 patients with Fontaine stage II PAD were treated with ESWT and demonstrated significantly improved maximum walking distance, shorter recovery time and improved walking impairment questionnaire scores [26].

### Aims and objectives

This study aims to compare the effects of extracorporeal shockwave therapy (ESWT) to the use of a sham control group on walking distances in subjects with lower limb intermittent calf claudication.

#### Primary outcome

The primary outcome is the effect of extracorporeal shockwave therapy in comparison to sham treatment on the maximum walking distance (MWD) — the distance covered before the subject is unable to continue — at baseline and at 4 weeks, 8 weeks and 12 weeks post therapy.

#### Secondary outcomes

The secondary outcomes are as follows:Claudication distance, i.e. distance covered prior to onset of any symptoms, at baseline and at 4 weeks, 8 weeks and 12 weeks post therapyAnkle-brachial pressure index (ABPI), measured at baseline and at 4 weeks, 8 weeks and 12 weeks post therapyPatient reported walking distance at baseline, 4 weeks, 8 weeks and 12 weeks post therapyQuality of life as measured by Short Form 36 questionnaire (SF-36) at baseline, 4 weeks, 8 weeks and 12 weeks post therapyQuality of life as measured by the EuroQol 5 domains questionnaire (EQ-5D) at baseline, 4 weeks, 8 weeks and 12 weeks post therapySubject tolerance of treatment, measured by VAS after each individual treatment session

### Design

This is a single-centre, double-blinded randomised controlled trial comparing extracorporeal shockwave therapy (ESWT) to sham treatment in the management of intermittent calf claudication.

### Setting

The trial will be conducted in the Academic Vascular Surgical Unit of the Hull York Medical School, based at Hull Royal Infirmary (University Teaching Hospital). All procedures will be performed in an outpatient-based or day-case setting.

### Patient identification

Patients will be recruited from vascular outpatient clinics and assessed for inclusion by the research team against the listed inclusion and exclusion criteria. In order to achieve target sample size, all patients identified as suffering from PAD will be screened for inclusion.

### Target population and recruitment

#### Inclusion criteria

Patients will be included who:Have unilateral or bilateral intermittent calf claudication (stable for the last 3 months)Are able to give written informed consent to participate in the studyAre >18 years oldAre able to adhere to the protocol and attend all follow-up appointmentsAre currently receiving ’best medical therapy’ — antiplatelet and statin medication

#### Exclusion criteria

Patients will be excluded if they:Currently have a malignancyAre allergic to or intolerant of either antiplatelet medication or statin therapyAre pregnant (pregnancy test performed at screening if necessary)Have a metal implant near the treatment areaAre taking anticoagulation medication (i.e. warfarin)Are diagnosed with a blood clotting disorder

### Screening and evaluation

Patients identified as potential participants will undergo a screening interview.

Baseline data will be collected from all consenting participants. Data collected will include:Evaluation of compliance with inclusion and exclusion criteriaIssue of Patient Information Sheet if not already issued
Informed consent (24 hours later)Participant’s name and address and, if used by the participant, mobile telephone number and email address (for the receipt of follow-up questionnaires) and date of birthDetails on participant’s general practitionerDemography and medical historyPhysical examination to include palpation of lower limb pulsesAnkle-brachial pressure index (ABPI)Vital signsAssessment of any concurrent medicationsPregnancy test if necessaryBody mass index (BMI)Smoking historyBaseline quality of life

Appropriately screened and consented individuals will be further assessed as follows:Baseline visitPatient reported walking distance (PRD)Vital signsQuality of lifeTreadmill assessment to report intermittent claudication distance (ICD) and maximum walking distance (MWD)For treadmill walking distances, ICD and MWD will be measured on a treadmill at 2.5 km/h at a 10° incline for up to 10 minutes. Participants will be asked to rest for 30 minutes prior to testing to ensure a resting state and negate effects of mobilising to the vascular laboratory.Randomisation will occur at the end of the baseline visit via sealed envelope software to either active treatment or control group by a second investigator. The treatment will then proceed as follows:(e)The second investigator will then perform ESWT therapy for the active group and sham treatment for the control group. Sham treatment will be delivered by setting the generator to off and replicating the sound of the active treatment via an audio recording emitted from the machine(f)All patients will then complete a tolerability questionnaire for the ESWT treatment.

Weeks 1, 2, 3 visitsVital signsESWT performed by second investigator with pulsewave generator on for active group and off for control groupPatient to complete tolerability questionnaire for ESWT treatmentPRD recordedAssessment of any concurrent medicationsAssessment of any adverse events
Week 4, 8, 12 visitsPRDVital signsQuality of lifeTreadmill assessment to report ICD and MWDAssessment of any concurrent medicationsAssessment of any adverse events

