### Outcome measurements

#### Primary outcome

The primary outcome is the short-to-medium term effect of ESWT in comparison to sham treatment on MWD in patients suffering intermittent calf claudication at baseline, 4 weeks, 8 weeks and 12 weeks post therapy.

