### Statistical considerations

Statistical advice has been sought from the Statistical Consultancy Service (Hull York Medical School, University of York) in preparing this protocol. Further review will be sought when all results have been collected and the analysis performed.

Data will be analysed as intention to treat. The SPSS computer package will be used with a *p* value of <0.05 taken as the level of significance.

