#### Sample size calculation

A power calculation will be performed from the ongoing cohort study and existing evidence with a maximum of 100 participants in total.

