#### Analysis

Data will be analysed on an intention-to-treat basis. The main aim is to provide estimates of distribution and variability of outcomes with comparisons made between the shockwave treatment group and sham group. These will be expressed principally as means or medians and confidence intervals.

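### The primary outcome, maximum walking distance, is defined without a limit but cannot be recorded above 416.7 m, so a difference in means would understate a benefit if participants reach that limit

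*Protocol article*

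**What the plan says.** All references are to the protocol article.

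- **Definition.** Under Aims and objectives, Primary outcome, MWD is "the distance covered before the subject is unable to continue". No limit is attached. The Outcome measurements section restates the outcome, again without one: "The primary outcome is the short-to-medium term effect of ESWT in comparison to sham treatment on MWD".
- **Measurement.** Screening and evaluation sets the test: "ICD and MWD will be measured on a treadmill at 2.5 km/h at a 10° incline for up to 10 minutes". The treadmill assessment is repeated at weeks 4, 8 and 12, and no other test is described.
- **Eligibility.** The inclusion and exclusion criteria require stable calf claudication but set no upper walking distance. The baseline treadmill test comes before randomisation, and its result excludes nobody.
- **Analysis.** The Analysis section says of the outcomes and their comparison between arms: "These will be expressed principally as means or medians and confidence intervals". It does not mention values recorded at the time limit.
- **Size.** The Sample size calculation section gives only a ceiling: "A power calculation will be performed from the ongoing cohort study and existing evidence with a maximum of 100 participants in total". No effect size, SD or distribution of MWD is given.

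**The concern.** The definition and the measurement do not describe the same quantity. A participant who is stopped by the clock has not become unable to continue. All that is known is that the true MWD exceeds 416.7 m. Because nothing in the eligibility criteria keeps participants away from the limit, this can happen at follow-up and also at baseline. Someone who completes the baseline test can later show deterioration on the primary outcome but not improvement.

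The consequence depends on the summary chosen. If treatment lengthens walking distance, more of the active arm than of the sham arm reaches the limit. Averaging the recorded distances as though they were MWD then removes more distance from the active arm. What is at stake is the primary estimate: a benefit reported in metres as smaller than it is, under a label that tells the reader no limit applied.

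**Working it through.** **1. The limit.** Speed x time = 2500 m/h x 10/60 h = 416.7 m. The article states no distance limit, sample size or effect, so there is no figure of its own to reproduce.

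**2. Direction.** Let S1 and S0 be the proportions still walking at each distance in the active and sham arms. The true mean difference is the area between S1 and S0 over all distances; the recorded one is that area from 0 to 416.7 m only. If treatment shifts the whole distribution upwards, S1 is never below S0, so the recorded difference cannot exceed the true one.

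**3. Size, under assumptions.** Take log-normal MWD with sham median m, log-SD s, an active/sham ratio r and limit c = 416.7. With mu = ln(median):

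- true mean = exp(mu + s²/2)
- share at the limit = 1 - Phi((ln c - mu)/s)
- recorded mean = exp(mu + s²/2) x Phi((ln c - mu - s²)/s) + c x (share at the limit)

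Worked example, m = 200 m, s = 0.6, r = 1.3:

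- Sham: true mean 239.4 m, 11% at the limit, recorded mean 221.7 m.
- Active (median 260 m): true mean 311.3 m, 22% at the limit, recorded mean 268.6 m.
- True difference 71.8 m; recorded difference 46.9 m; ratio 0.65.
- Difference in medians: 260 - 200 = 60 m with or without the limit.

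All twelve scenarios:

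| Sham median (m) | log-SD | Ratio | Sham at limit | Active at limit | True diff. (m) | Recorded diff. (m) | Recorded/true |
|---|---|---|---|---|---|---|---|
| 100 | 0.6 | 1.3 | 1% | 3% | 36 | 34 | 0.94 |
| 100 | 0.6 | 1.5 | 1% | 4% | 60 | 55 | 0.92 |
| 100 | 0.8 | 1.3 | 4% | 7% | 41 | 33 | 0.79 |
| 100 | 0.8 | 1.5 | 4% | 10% | 69 | 52 | 0.76 |
| 150 | 0.6 | 1.3 | 4% | 10% | 54 | 44 | 0.81 |
| 150 | 0.6 | 1.5 | 4% | 15% | 90 | 69 | 0.77 |
| 150 | 0.8 | 1.3 | 10% | 17% | 62 | 38 | 0.62 |
| 150 | 0.8 | 1.5 | 10% | 22% | 103 | 60 | 0.58 |
| 200 | 0.6 | 1.3 | 11% | 22% | 72 | 47 | 0.65 |
| 200 | 0.6 | 1.5 | 11% | 29% | 120 | 72 | 0.60 |
| 200 | 0.8 | 1.3 | 18% | 28% | 83 | 40 | 0.48 |
| 200 | 0.8 | 1.5 | 18% | 34% | 138 | 61 | 0.44 |

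**4. The same by share at the limit.** With log-SD 0.5 or 0.7 and the same two ratios, the recorded mean difference falls short of the true one by 1-2% when 0.1% of the sham arm is at the limit, 6-10% at 1%, 19-27% at 5%, 31-39% at 10%, 47-57% at 20% and 78-84% at 50%.

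**5. Medians.** An arm's median is unchanged until about half of that arm is at the limit. The largest share in the table is 34%, so no median difference there is affected. Once both medians sit at 416.7 m, the difference is zero.

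**6. Power.** Taking 50 per arm (half of the stated maximum of 100) and assuming a two-sided 0.05 level, since the article does not state sidedness, power for a comparison of raw means is higher with the limit than without it in all twelve scenarios. For example, it moves from 0.50 to 0.56 for m = 150 m, s = 0.6, r = 1.3. The limit shrinks the SD as well as the difference. Power falls only under heavy capping: from 0.68 to 0.58 with half of the sham arm at the limit, log-SD 0.5 and r = 1.3.

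**The case against.** The strongest reply is that the article does not commit to means. Medians are equally permitted, and at the capping levels assumed here they give the right answer. Rules for values at a measurement limit also commonly sit in a full protocol or statistical analysis plan, and neither is shown. Both points stand. The silence on handling cannot be read as a decision to treat 416.7 m as a true distance. What remains is on the page: the stated outcome and the stated test disagree, and the summary that suffers from the disagreement is allowed.

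A reader might infer more than the article supports:

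- **That the treatment effect is biased towards zero outright.** This needs a real benefit, participants at the limit, and a comparison by means. With no effect there is nothing to shrink.
- **That power is lost and a real effect may be missed.** The calculation does not show this; at moderate capping power on raw means goes slightly the other way.
- **That participants who complete the baseline test should no longer be randomised.** This does not follow. It would change the population during recruitment, and those participants can still show deterioration in MWD and change in claudication distance, patient-reported distance and quality of life.

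It is also fair to say that mean distance walked within 10 minutes is a legitimate quantity. It is just not the one the article defines.

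**Conclusion.** The point holds in a limited form. The 416.7 m limit and its conflict with the definition of the primary outcome are certain, and need only the article's own speed and time. That a difference in means would understate a benefit is conditional on treatment shifting distances upwards and on some participants completing 10 minutes.

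The size is not known from the article. Under the log-normal assumptions above, the recorded mean difference is 76-94% of the true one for a sham median of 100 m and 44-81% for medians of 150-200 m. It approaches 100% if almost nobody reaches the limit. The harm is to the size of the primary estimate when means are used; the difference in medians is safe unless about half of an arm is at the limit.

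**What to change.** Keep the treadmill test and the eligibility criteria as they are.

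1. Reconcile the Primary outcome sections with Screening and evaluation: define the outcome as MWD within a 10-minute test, with participants still walking at 10 minutes censored at 416.7 m.
2. Add a case report form flag for completing the 10 minutes, and report the number flagged by arm and visit, including baseline.
3. In place of a plain difference in means, prespecify one comparison that respects the limit: a censored (Tobit-type) regression of log MWD on arm and baseline; time to stopping with completers censored; or medians or ranks. The choice is a matter of judgement: the regression leans on the log-normal shape, and medians need fewer than about half of each arm at the limit.
4. Label any mean still shown as mean distance walked within the 10-minute test.

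The cost is a change of wording, one data flag and slightly more analysis work. The Trial status section says recruitment was still under way, so the choice could be fixed before the results are analysed.
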